### Eligibility and exclusion criteria for participants

Eligibility criteria of participants in this research include: (1) biologically male, (2) have oral or anal sex with men at least once during their lifetime, (3) aged 15 years or older, (4) have no difficulty using a mobile phone, (5) willing to provide their mobile phone numbers to serve as the unique identification numbers of the app’s self-query and partner notification functions, (6) willing to use the app’s function modules, (7) willing to complete the questionnaire for the research, (8) willing to continuously receive HIV and STDs testing and consulting services provided by the CBO our research setting at, and (9) willing to complete the informed consent document. MSM who had serious physical disabilities or mental diseases will be excluded.

MSM who meet all the eligibility criteria, but whose first HIV test results are positive, will also be invited to register as app users and complete the questionnaire. However, they will not be included in the statistical analysis of HIV incidence and other outcomes except for social network related outcomes.

### Interventions

#### Tools of interventions

The tools of interventions contain a WeChat official account and an app with four functional modules centering on partner notification.

The WeChat official account is developed with three functions. First, it can be used as a service platform to provide the online “Mailing rapid test reagent kit” self-testing service. Participants can make an appointment of HIV and STDs rapid test reagent kit through it. Second, health education materials can be sent to participants through the WeChat notification messages weekly. Third, it can be a medium for participants logging in the app. We set a link to the app at the WeChat official account, so participants can easily and quickly to use the functional modules of the app. (Additional Fig. 1).

The app we develop for this research named *Golden ark*, which contains four functional modules, including partner notification module, test result self-query module, prompt and warning module, and health education module. The functions of these modules are as follows [29].

### Partner notification module

This module allows users to request each other’s recent HIV and other STDs status and the test date from the CBO’s database. To be ethical and privacy-protecting, the applicant should be permitted by those the applicant requests for. The framework of the partner notification (User 1 requests the status of User 2) contains four steps: (1) User 1 requests User 2’s HIV and other STD’s status by using User 2’s phone number through the app. (2) System center (CBO’s database) will convert the request as a message that can be confirmed and approved by User 2 through App. (3) User 2 deals with the request with “Agree” or “Disagree”, and send it back to the system center. (4) If User 2 agrees to inform User 1, system center will return User 2’s recent HIV and other STD’s test results and the date of the testing to User 1. If not, return “The request was denied”. (Fig. 2, Additional Fig. 2).

**Fig. 2 Fig2:**
[figure not shown]
The framework of the partner notification

### Test result self-query module

After completing HIV and STD testing, CBO’s staff will upload the test results and dates into the database, so users can query their own test results and dates through the app’s test result self-query module. (Additional Fig. 3).

### Prompt and warning module

In addition to some fixed prompts and warnings for information security concern, this module also provides some dynamic prompts and warnings based on their own test records and the responses of partner notification they received. For their own test records, the users will receive prompts to encourage them to have HIV and STDs testing monthly through app as well as mobile phone short messages according to the dates of their last test records. For partner notification, based on the User 2’s response and infection status shown as follows, the app will send different prompts and warnings to protect User 1 from the potential risks. (Fig. 3, Additional Figs. 2, 3).

**Fig. 3 Fig3:**
[figure not shown]
Types of request results and corresponding warning messages

### Health education module

In this module, health education materials will be sent to participants weekly through the WeChat official account. An additional function of this module is that the history records of health education materials can be classified and saved in the module, so users can review the materials when they need any time. (Additional Fig. 4).

#### Intervention implementation

Based on the CBO’s existing HIV and STD prevention methods, such as HIV and STDs testing services, we construct a new integrated intervention model for HIV and STDs control among MSM by adding two parts of interventions.

The first part is to strength MSM’s safety awareness of seeking sexual partners and sense of health self-responsibility. Two measures will be implemented as follows: (1) Provide health education materials weekly to participants through the WeChat official account and app’s health education module. These materials contain the harmfulness of HIV/AIDS and STDs, symptoms and signs of HIV/AIDS and STDs, awareness of receiving HIV and STDs testing on their own initiative, awareness of partner notification, HIV/AIDS and STDs prevention skills, related laws, related drug use instruction, and the harmfulness of drug abuse and its prevention. The content of health education will repeat every 6 months in order to ensure all participants receive the whole education content. (2) Provide HIV and STDs testing prompting service to HIV negative participants monthly according their test records individually through app’s prompt and warning module and mobile phone short messages.

The second part is to promote and encourage partner notification through the app. We expect if two MSM are dating through some online dating platforms, the partner notification and related warnings provided via the app will in a timely manner help them know each other’s HIV and STDs status before they are going to meet and have sex.

This research is designed as a pragmatic SW-CRCT study. The interventions participants received in the control period and the intervention period are different. In control period, they will receive health education through the WeChat official account and app, as well as HIV and STDs testing prompting service. The app’s test result self-query module is also opened to them to promote the use of the app and avoid the loss to follow-up. But the partner notification is not available. In intervention period, all interventions in the control period will continue, and the partner notification functions will be opened. (Fig. 1).

### Randomization and allocation

The randomization is conducted in cluster (district) level, instead of individual level. The previous records of the CBO show that most MSM receiving HIV testing services are from the following four districts: Chaoyang, Shunyi, Fengtai, and Haidian. Considering the number balance of participants in each groups, stratified randomization is used. The process of randomization is conducted by a researcher using SAS software: (1) Assign each district a number, A1 to A4 for the four districts that the research may recruit more potential participants (Chaoyang, Shunyi, Fengtai and Haidian), B1 to B12 for other twelve districts. (2) Extract without putting it back one number in districts A and three numbers in districts B to be one sampling group. Finally, the sixteen districts will be randomized into four intervention groups. (3) Randomize the order of four intervention groups to be Group 1 to 4, and the additional partner notification intervention using app will be implemented to these groups in sequence every 6-month intervals. The participants will be assigned to different groups according to the district where they live recorded in the baseline questionnaire.

As the partner notification is a kind of behavioral intervention, it is impossible that participants do not know what intervention they receive. So, the research is only single-blind to outcome assessors. However, we take efforts to reduce the information bias caused by the non-blind design of other stakeholders. At the beginning of the research, participants, staff of the CBO, and the researchers who participate in management of participants will not know the randomized scheme of the research. The additional partner notification will be opened to participants sequentially by the predetermined computer program, which does not need CBO staffs and researchers to implement the intervention manually. The CBO staffs and researchers do not know the implementation of partner notification unless the participants tell them whether they can use the partner notification function of the app on their own initiative. Even the CBO staff knows that, the operation and results of the HIV and STDs testing will not be affected. Also, the outcomes assessors do not know the randomized scheme in the process of data analysis.

### HIV and STDs testing

HIV and STDs testing will be conducted at baseline investigation during participants recruitment, and follow-up investigations by CBO staffs. There are two alternative ways that participants can receive testing services, including the “Mailing rapid test reagent kit” self-testing service and the facility-based testing service.

The “Mailing rapid test reagent kit” self-testing service bases on participants’ applications on the WeChat official account. The procedures for one participant applying for HIV and STD self-testing are as followed: (1) Fill in phone number and address information used to mail the test kit through the WeChat official account; (2) The CBO will send a package of rapid test reagent kit to the user (the kit is free of charge, but the express fee charged by express company is required); (3) Complete the self-testing using the test kit by himself. If he does not know how to use, he can see a teaching video provided on the WeChat official account; (4) Take a clear picture of the test reagent kit and upload it to CBO through the system; (5) CBO’s trained staff will check the results and generate a testing report for the user showing the result “Negative” or “Positive” of HIV and STDs and the date of this testing service. (Fig. 4).

**Fig. 4 Fig4:**
[figure not shown]
Flow chart of the “Mailing rapid test reagent kit” testing service. (The images were drawn by the author team of this study)

For the facility-based testing service, when one participant comes to the clinic sites of the CBO for testing, the testing service will be implemented one-to-one by the CBO’s trained staff. After testing, the CBO’s staff will input the test results and date into the backend database, and the participant can get an electronic test result report.

In addition, if a participant’s HIV or other STDs’ test result is positive, the CBO staffs will contact him, help him confirm the disease status by referring him to the local Centers for Disease Control and Prevention (CDC) and provide him additional health care. The test reagent kit used in both “Mailing rapid test reagent kit” self-testing service and the facility-based testing service will be the HIV, HCV, TP, HBsAg quaternary Colloidal Gold reagent (Wondfo^@^).

### Sample size

We used the *steppedwedge* procedure in Stata software set for SW-CRCT design to calculate the sample size. We assumed the HIV incidence was 7% in the control status, and could be reduced to 5% after partner notification intervention. The parameters set for sample size calculation include: (1) The number of clusters was 16; (2) The number of steps was 4, with 4 clusters in one step; (3) α was set as 0.05; (4) Power was set as 0.90; (5) ICC (ρ) was set as 0.01. The total sample was 4320 (270 for each clusters). Considering most studies of MSM showed a high proportion of loss to follow up, we set a 30% loss to follow up in this research. The total sample size was 6172.

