## Methods/design

### Study design and timeline

This research will use a stepped wedge cluster randomized controlled trial (SW-CRCT) design. It is commonly used to evaluate service delivery or policy interventions of clusters [26]. This research will be implemented in Beijing, whose sixteen districts are defined as the clusters. We assign the sixteen districts into four research groups using stratified randomization, with four districts in one group. The open cohort SW-CRCT will last 2.5 years, which is anticipated to be conducted from July, 2020 to December, 2022. Five continuous observational periods at a 6-month interval are divided. According to the standard design of SW-CRCT, in the first 6-month “the initial period”, no group is exposed to the additional partner notification intervention. After that, the four groups begin to cross from the control condition to receive the partner notification intervention sequentially at 6-month intervals. Once one group receives the partner notification intervention, the intervention will continue until the end of the research. And at the last 6-month period, all of the four groups will receive the additional partner notification intervention. (Fig. 1).

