### Study setting and recruitment

We will conduct our research in Beijing, the capital city of China with high population mobility and demographic heterogeneity and high burden of HIV and related STDs among MSM. We will cooperate with a local community-based organization (CBO) named *Man Wellness Center* to recruit participants and provide HIV and other STDs (syphilis, hepatitis B, and hepatitis C) testing services. *Man Wellness Center* is one of the largest and most popular CBO for MSM to give them HIV and STDs prevention and medical services.

Participants will be recruited in two ways: offline and online. The offline recruitment will be implemented in offline venues, such as the clinic sites of the CBO for routine work, and the gay bars, bathrooms, parks for outreach services. The online recruitment will be implemented through online platforms, such as WeChat, QQ, Weibo and Blued. The process of recruitment includes four steps: (1) Determine whether the participant recruited meets the eligibility criteria. (2) Introduce the research and tools for interventions (the app and the WeChat official account) if eligible. (3) Help the participant sign the electronic informed consent through the app and then show him the functions of the app and WeChat official account. The content of the electronic informed consent contains all necessary information as traditional paper version of informed consent, and the signed electronic informed consent will be stored in the database. Participants under the age of 18 are asked to register the app system and sign the consent accompanied by a guardian, and written consent is also obtained from the guardian. (4) Invite the participant to fill in the baseline questionnaire through the app. (5) Provide HIV and other STDs testing services and upload the test results through the backend database. The recruitment will start from the beginning of the research, and we will stop recruitment in the last 6 months of the research. If the participant has HIV and other STDs testing during the follow-up period, he will be invited to finish a follow-up questionnaire.

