### Outcomes

The primary outcomes of this research are the HIV positive seroconversion rate (HIV incidence) and the additional cost of the intervention. The HIV positive seroconversion rate is calculated as the number of HIV positive seroconversions divided by the total number of person-years. The additional cost of the intervention is calculated as the total cost and average cost for per participant of the integrated intervention model and each additional intervention/service based on the existing HIV prevention measures provided as before.

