## Discussion

One important reason that HIV keeps increasing among MSM in China is that most MSM seeking causal sexual partners through online dating platforms (such as Blued and Zank), as it results in much more risk sexual behaviors for HIV and other STDs transmission [30, 31]. Partner notification of HIV and STDs infection statuses before they decide to meet and have sex can be an important and feasible method to reduce the HIV and STDs transmission among sexually active MSM. China’s Internet penetration rate has reached 61.2% by June 2019, and 99.1% of Internet users use mobile phones to surf the Internet [32]. The intervention tools based on the WeChat-the most popular mobile phone social software [33], and a website-based app enable the method more acceptable, convenient and intimate for MSM. It may lead to better effects compared with the existing partner notification methods provided by health workers individually or through email cards. An observational study using the previous version of this app has shown a potential positive effect of the app-based partner notification intervention in reducing HIV infection among MSM [29]. An encouraging finding was that the longer the app was used, the lower the HIV incidence (> 5 months vs ≤ 5 months: 2.22 per 100 person-years vs 6.99 per 100 person-years; risk ratio 0.32, 95% CI 0.12–0.87), and the app has also been proved to be user-friendly and could be accepted and widely used by MSM [29]. However, the blank control without receiving the partner notification intervention was lacking in the observational study. Meanwhile, the observation period was only 1 year and the sample size was small, so the effectiveness of the intervention needs to be further evaluated by this trial.

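### The 90% power stated for 4320 men holds only if 7% and 5% are 6-month risks and every district is at full size in all five periods; the rest of the protocol points to annual rates and gradual recruitment

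*Protocol article*

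**What the plan says.** The Sample size section of the protocol article gives the effect as "We assumed the HIV incidence was 7% in the control status, and could be reduced to 5% after partner notification intervention". It does not say over what length of time. The other inputs are "The number of clusters was 16", "The number of steps was 4, with 4 clusters in one step", α 0.05, power 0.90 and an ICC of 0.01. The result is "The total sample was 4320 (270 for each clusters"; allowing for 30% loss raises this to 6172.

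Four other places bear on how those inputs should be read:

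- Study design and timeline: "Five continuous observational periods at a 6-month interval are divided", in an open cohort lasting 2.5 years.
- Study setting and recruitment: "The recruitment will start from the beginning of the research, and we will stop recruitment in the last 6 months of the research".
- Outcomes: the primary HIV outcome is "the number of HIV positive seroconversions divided by the total number of person-years".
- Discussion: the observational study of the previous version of the app found "2.22 per 100 person-years vs 6.99 per 100 person-years" for longer against shorter use. The Background section cites 8.5 and 2.0 per 100 person-years for users and nonusers of dating apps.

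**The concern.** A stepped-wedge formula for a proportion works with the risk in one period and the number of men observed in each cluster in each period. Here a period is 6 months. If annual incidences are entered as period risks, both the expected events per period and the absolute difference are about twice what the trial will see. If, in addition, 270 men per district are assumed from the first day while men are in fact recruited over 24 months, the early periods hold far less information than the calculation credits. The first period matters because it is the only one in which all districts are in the control condition.

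HIV incidence is a primary outcome, and the trial is meant to guide policy. If power is well below 90%, a non-significant result could be read as evidence against partner notification when the design had a substantial chance of missing the planned effect.

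**Working it through.** **Inputs.** 16 clusters, 4 sequences of 4 clusters, 5 periods, ICC ρ = 0.01, 7% against 5% (Sample size); two-sided 0.05 (Analysis); 6-month periods (Study design and timeline).

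**Formula.** Stepped-wedge model with fixed period effects and a random cluster effect. Let s = p₁(1 − p₁), σ² = s(1 − ρ)/m and τ² = ρs, with m men per cluster in each period. For this layout the variance of the effect reduces to

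Var = σ²(σ² + 5τ²) / (10σ² + 30τ²), and power = Φ(δ/√Var − 1.96).

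**Step 1: reproduce the stated figure.** With p₁ = 0.07, s = 0.07 × 0.93 = 0.0651. At m = 270:

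- σ² = 0.0651 × 0.99/270 = 0.0002387 and τ² = 0.000651.
- Var = 0.0002387 × 0.0034937/0.021917 = 0.00003805, so SE = 0.00617.
- δ/SE = 0.02/0.00617 = 3.242, and power = Φ(1.282) = 0.9001.

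At m = 269 power is 0.8991, so 270 is the smallest size that reaches 90%. Then 270 × 16 = 4320, and 4320/0.70 = 6171.4, rounded up to 6172. If 270 were instead the cluster total, 54 per period, power would be only 34% (38% with the average of the two arms' variances). The stated figure therefore takes 7% and 5% as risks in each period and 270 as a cluster-period size.

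**Step 2: put the incidences on the 6-month scale.** A 6-month risk of 7% is about 2 × 7 = 14 per 100 person-years, above every HIV incidence the protocol cites. Read as annual, 7 and 5 per 100 person-years give about 3.5% and 2.5% per 6 months. With s = 0.035 × 0.965 = 0.033775 and m = 270:

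- σ² = 0.00012384 and τ² = 0.00033775.
- Var = 0.00001974, so SE = 0.00444.
- δ/SE = 0.01/0.00444 = 2.251, and power = Φ(0.291) = 0.614.

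Using the average variance of the two arms gives 0.679.

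**Step 3: allow for recruitment.** The protocol gives a recruitment window but no curve. *Assumption:* even entry over months 0-24. The average share of the cohort present is then 12.5%, 37.5%, 62.5%, 87.5% and 100% in periods 1 to 5. That sums to 3.0 full periods against the 5.0 the calculation assumes. The same model was refitted with these cluster-period sizes. In each cell below, the lower figure uses the control variance and the higher the average variance.

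| Risks per 6 months | Cohort | 4320 (270 per district) | 6172, no loss (386 per district) |
|---|---|---|---|
| 7% vs 5% | full in all periods | 90-94% | 97-99% |
| 7% vs 5% | even entry, 24 months | 72-78% | 85-90% |
| 3.5% vs 2.5% | full in all periods | 61-68% | 76-82% |
| 3.5% vs 2.5% | even entry, 24 months | 42-48% | 55-61% |

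**Step 4: sensitivity, at 3.5% against 2.5% and 4320 men.**

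- Shares present of 25/50/75/100/100% give 48-54%.
- Half the cohort present in period 1 and all of it afterwards gives 59-65%.
- Exact conversion of the rates to 6-month risks (3.44% and 2.47%) moves the full-cohort, average-variance figure from 68% to 66%.
- An ICC between 0.005 and 0.05 keeps that figure at about 66-69%.

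**The case against.** The strongest defence is that the Sample size section never calls 7% and 5% annual. If they were meant as 6-month risks, the calculation agrees with its formula. That stands as a matter of wording: the annual reading is an inference. It is a strong one, because the outcome is per person-year, the cited HIV incidences are all per 100 person-years, and 6.99 is almost exactly the 7% assumed. The defence also does not rescue the 90%: with even recruitment, 7% against 5% per period gives 72-78% for 4320.

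Second, a reader might infer that the true power is about one half. The documents do not support a single figure. The accrual curve is assumed; faster entry gives clearly better power. The 4320 basis also gives men who are later lost no person-time, although under a person-year outcome they contribute until they leave. The 6172 basis errs the other way, because it assumes no loss. The answer for a given curve lies between the two columns.

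Third, a calculation on the rate scale would suit the outcome better than halving the risks. That is fair, but its result depends on the between-district variance on that scale, which the protocol does not give. The figures here stay with the protocol's own ICC for that reason.

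**Conclusion.** The 90% statement is wrong as written. It requires period risks of 7% and 5% and full cohorts in every district from the first period. The first condition conflicts with the scale of the outcome and of the cited incidences, and the second with recruitment that continues until the last 6 months.

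Taking the rates as annual, the mismatch in time unit alone lowers power for 4320 men from 90% to 61-68%. This is the firmest figure, since it needs no accrual assumption. Gradual recruitment lowers it further, to 42-48% if entry is even. None of the annual-rate settings examined reaches 90%, even with all 6172 men present throughout and none lost (76-82%). With full cohorts, 90% would need about 492 to 573 men per cluster-period, that is 492 × 16 = 7872 to 573 × 16 = 9168 before allowing for loss.

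These conclusions rest on the annual reading, the protocol's ICC of 0.01 and, for the lower figures, the assumed recruitment curve.

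**What to change.** In the Sample size section:

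1. State the time unit of 7% and 5%. If they really are 6-month risks, justify an incidence of about 14 per 100 person-years.
2. State that 270 is the number of men under observation per district in each period.
3. Recalculate power from 7 against 5 per 100 person-years, using the person-time expected in each district and period under a declared recruitment curve and loss pattern, and declare the between-district variance used.
4. Replace the 90% statement with the resulting power and the rate ratios detectable at 80% and 90%.

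The cost is a recalculation, a rewritten paragraph and a less favourable stated power; the correction itself needs no extra participants. Earlier recruitment would help, but it should not be presented as a free remedy: the protocol recruits through one community organisation over 24 months, and nothing in it shows that a faster pace is feasible. Nor would it restore 90% on annual rates, since even full cohorts from the first day do not.

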**Methods:**

A pragmatic stepped wedge cluster randomized controlled trial design is used to evaluate the effectiveness of a new intervention paradigm, which aims to reduce HIV and other STDs incidences among MSM in China. Through integrating a mobile health (mHealth) service application (app) to the current HIV and other STDs prevention and control methods, the new paradigm provides partner notification of HIV, syphilis, hepatitis B, and hepatitis C statuses. A total of 6172 MSM in 16 districts of Beijing, China will be recruited and randomized to sequentially receive partner notification intervention through the app at 6-month intervals. The primary outcomes are HIV incidence and the additional cost of the intervention. The secondary outcomes include incidences of syphilis, hepatitis B, and hepatitis C, disease transmission social networks, testing adherence, knowledge of HIV and STDs control, health self-responsibility awareness, changes of high risk behaviors and other related outcomes. The generalized linear mixed models (GLMM) will be used to analyze the differences of outcomes in the control period and in the intervention period.

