If the participant is recruited offline, to protect the participants’ privacy and confidentiality, the process of the recruitment will be implemented one-to-one by the CBO’s trained staff in a private environment. If the participant is recruited online, the process will also be implemented one-to-one through online platforms. After finishing the baseline questionnaire, the participant will be suggested to use the HIV and STDs self-testing services or go to the CBO clinics to receive facility-based testing. If the online recruited participant does not conduct the testing 1 month after registering, he will receive testing reminding information through the app and mobile phone short message.

Ethical Approval for this study has been obtained from the Peking University Institutional Review Board (IRB00001052–16016).

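### The target of 6172 allows only for 30% loss to follow-up, although men positive at the first HIV test are recruited and then left out of the incidence analysis

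*Protocol article*

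**What the plan says.** The Methods paragraph of the abstract gives the target as a number of men recruited: "A total of 6172 MSM in 16 districts of Beijing, China will be recruited and randomized".

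The Sample size section starts from 4320 men (270 per district) for 90% power at α 0.05 and ICC 0.01. Its effect assumption is "We assumed the HIV incidence was 7% in the control status, and could be reduced to 5% after partner notification intervention". It makes one adjustment, justified by the high loss seen in studies of MSM: "we set a 30% loss to follow up in this research. The total sample size was 6172".

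The section on eligibility and exclusion criteria lists nine criteria, none of which is a negative HIV test. Men who meet all of them but are positive at the first test are still invited to register and complete the questionnaire. Of these men it says: "they will not be included in the statistical analysis of HIV incidence and other outcomes except for social network related outcomes".

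The section on study setting and recruitment puts consent and the baseline questionnaire (steps 3 and 4) before testing (step 5).

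**The concern.** The target counts men who are recruited. The primary outcome, HIV seroconversion per person-year, can come only from men who are negative at a first test and are then followed. Men positive at the first test belong to the first group and, by the plan's own rule, not to the second. Their exclusion is planned and happens at baseline, so it is different from loss to follow-up, and the Sample size section makes no allowance for it.

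At stake is whether a trial that meets its recruitment target and loses exactly 30% has the number of men on which its stated power rests. If recruitment is tracked by registrations, the target could be reported as met while the set for the primary analysis is short.

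**Working it through.** **Inputs from the article.** 7% against 5%, ICC 0.01, α 0.05, power 0.90, 4320 men (270 × 16), 30% loss and 6172 come from the Sample size section, as do "The number of clusters was 16" and "The number of steps was 4, with 4 clusters in one step". The Analysis section gives two-sided testing. The design section gives the number of periods: "Five continuous observational periods at a 6-month interval are divided".

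**Assumed input.** The share positive at the first test, p, is not given. I use 2%, 5%, 10% and 15%.

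**Step 1: the plan's inflation.** 4320/(1 − 0.30) = 6171.4, rounded up to 6172. In reverse, 6172 × 0.70 = 4320.4. Nothing is left over: with one recruit fewer, 6171 × 0.70 = 4319.7.

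**Step 2: the plan's 270.** I used the Hussey–Hughes variance for a stepped wedge with I = 16 districts and T = 5 periods:

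Var = I·e·(e + T·τ²) / [(I·U − W)·e + (U² + I·T·U − T·W − I·V)·τ²]

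- The design sums are U = 40, W = 480 and V = 120, so I·U − W = 160 and the second bracket is 480.
- With the control-arm variance, σ² = 0.07 × 0.93 = 0.0651 and τ² = 0.01 × 0.0651 = 0.000651.
- With 270 men per district and period, e = 0.99 × 0.0651/270 = 0.0002387.
- The standard error is 0.006168, so 0.02/0.006168 = 3.242, and power = Φ(3.242 − 1.960) = 0.900.
- With 269 men power is 0.899, so 270 is the smallest number that reaches 90%. This choice reproduces the plan's figure.

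**Step 3: men left after the exclusion.** Analysable men = 6172 × (1 − p) × 0.70. Power uses the model of step 2 with that number divided by 16. The number of recruits that would restore 4320 is 4320/(0.70 × (1 − p)), rounded up.

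| p (assumed) | Analysable men | Short of 4320 | Power | Recruits to restore 4320 |
|---|---|---|---|---|
| 2% | 4234 | 86 | 89.5% | 6298 |
| 5% | 4104 | 216 | 88.6% | 6497 |
| 10% | 3888 | 432 | 86.9% | 6858 |
| 15% | 3672 | 648 | 85.1% | 7261 |

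**Step 4: sensitivity to the variance choice.** With the average of the two arms' variances, (0.0651 + 0.0475)/2 = 0.0563, 270 per district and period gives 93.7%. Power is then 93.2%, 92.5%, 91.2% and 89.7% at 2%, 5%, 10% and 15%. Under this choice 232 per district and period is enough for 90%, and 16 × 232 = 3712 men remain available up to p = 1 − 3712/4320.4, about 14%.

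**Step 5: loss that would absorb the exclusion.** To keep 4320 men from 6172 recruits, loss could be at most 1 − 4320/(6172 × (1 − p)): 26.3% at p = 5% and 22.2% at p = 10%.

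**The case against.** The strongest reply is that the article never says men positive at the first test count toward 6172. It says they will also be invited, which can describe a group additional to the target and kept for the network outcomes. The abstract's background also presents the services as being for HIV-negative MSM. On that reading there is no shortfall. The reading is possible, but no sentence restricts 6172 to HIV-negative men, the abstract calls it the number recruited, and testing comes after consent and questionnaire. The ambiguity therefore stands and the text should settle it.

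A reader might infer that 6172 recruits cannot deliver 4320 analysable men. The documents do not support this. The cohort is open, recruitment stops by date (in the last six months) and not at a count, so more than 6172 men may register. Loss could also be below 30%, which is itself a round assumption.

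A reader might also add men who register online and never test, given the passage beginning "If the online recruited participant does not conduct the testing 1 month after registering". That passage describes a reminder and gives no expected rate of non-testing. Such men yield no follow-up and can fall within the 30% loss, so counting them separately risks double counting. I make no deduction for them.

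It is also fair to say that the effect on power is small and depends on the variance choice, as step 4 shows. In addition, 270 reproduces as a number per district and period, and whether the plan meant it so is a larger, separate question. Neither removes the mismatch between the men counted and the men analysed.

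**Conclusion.** The point holds as a minor mismatch in the stated sample size. The division by 0.70 is right, and this is not an arithmetic error.

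If men positive at the first test count toward 6172, following the plan exactly leaves fewer than 4320 men for the HIV incidence analysis. At an assumed 5% to 10% positive the gap is 216 to 432 men, and power falls from 90% to between 88.6% and 86.9%.

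This rests on three assumptions: the natural reading of what 6172 counts, a positivity that the article does not give, and 4320 giving exactly 90% power on the control-arm variance. If 6172 was meant as HIV-negative men only, the shortfall disappears and only the wording needs correcting.

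**What to change.** Choose one of two changes, made both in the Sample size section and in the Methods paragraph of the abstract.

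1. Define 6172 as men with a negative first HIV test, and monitor recruitment on that count. Somewhat more men must then be registered to reach it: about 6497 at 5% positive or 6858 at 10%, both assumed.
2. Keep 6172 as all registered men, state the assumed share positive at the first test, and restate the analysable number as 6172 × (1 − that share) × 0.70, with power to match.

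Either takes about a sentence and adds no study procedure. The first changes the counting rule in recruitment reports and needs slightly more registrations. The second makes the stated analysable number and power slightly less favourable.
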